## 1 Definitions and Abbreviations

|          |                                                   |
|----------|---------------------------------------------------|
| AE       | Adverse Event                                     |
| AKI      | Acute Kidney Injury                               |
| ALAT     | Alanine aminotransferase                          |
| Alb      | Albumin                                           |
| ASAT     | Aspartate aminotransferase                        |
| APTT     | Activated Partial Thromboplastin Time             |
| CE       | Conformité Européene                              |
| CNS      | Central Nervous System                            |
| Crea     | Creatinine                                        |
| CRRT     | Continuous Renal Replacement Therapy              |
| ELSO     | Extracorporeal Life Support Organization          |
| eGFR     | estimated Glomerular Filtration Rate              |
| FiO2     | Fraction of inhaled oxygen                        |
| g        | gram                                              |
| h        | Hour                                              |
| ICU      | Intensive Care Unit                               |
| ID       | Identification                                    |
| INR (PT) | International Normalized Ratio (Prothrombin Time) |
| KDIGO    | Kidney Disease: Improving Global Outcome          |
| l        | Liters                                            |
| MA       | Marketing Authorisation                           |
| mGFR     | measured Glomeruli Filtration Rate                |
| min      | minute                                            |
| ml       | milliliter                                        |
| n        | nano                                              |
| U-NAG    | Urine - N-acetyl-β-D-glucosaminidase              |
| P        | Plasma                                            |
| PaCO2    | Partial pressure of carbon dioxide in artery      |

|                  |                                      |
|------------------|--------------------------------------|
| PaO 2 | Partial Pressure of Oxygen in Artery |
| PfHb             | Plasma Free Hemoglobin               |
| SAE              | Serious Adverse Event                |
| SAP              | Statistical Analysis Plan            |
| S                | Serum                                |
| TNI/TNT/T        | Troponin I/T                         |
| U                | Urin                                 |

A second randomized, blinded, clinical trial to study the safety and efficacy of PrimeECC® was performed at Sahlgrenska University Hospital, Gothenburg, Sweden, during 2016 and 2017. This study included 39 + 41 patients undergoing cardiac surgery with ECC and compared priming with PrimeECC® to Ringers acetate with mannitol. Patients with known severe kidney or liver disease, malignancies, sepsis, systemic inflammatory disease or bleeding disorder were excluded. The primary endpoint was oncotic pressure during ECC, with fluid balance and organ function as secondary endpoints. In the PrimeECC® group, the oncotic pressure was higher during and early after ECC, and the patients received less intravenous fluids. In addition, the PrimeECC-patients had significantly less postoperative renal tubular injury measured as urinary N-acetyl-β-D-glucosaminidase (NAG), and reduced levels of hemolysis measured as free plasma-hemoglobin. The study revealed no significant differences in perioperative liver- and lung function, AKI, bleeding, use of blood products or cerebral or myocardial injury markers.

In summary, the use of PrimeECC® has been associated with improved perioperative fluid balance, reduced tubular cell injury and reduced hemolysis. However, the studies have been underpowered to detect clinical endpoints such as postoperative AKI and there is no additional published data available on the direct comparison of colloidal and crystalloid priming solutions in ECC for cardiac surgery. The present study is designed to investigate if priming with PrimeECC®, compared to crystalloid solution, will lead to a reduced incidence of AKI in a group of elective cardiac surgery patients identified to be at high risk for post-operative kidney injury. As secondary outcomes, incidence of renal replacement therapy, NAG-excretion and estimated glomerular filtration rate (eGFR) will be evaluated. Furthermore, the level of hemolysis and myocardial and CNS injury biomarkers will be assessed.

### 3 Pre-clinical data

Preclinical testing of PrimECC® was done in a porcine model, however, the results were not published due to proprietary reasons. Sixteen pigs of about 60 kgs were randomized to evaluate the differential hemodynamic effects of priming the ECC with PrimECC® versus crystalloid (non-oncotic) solution. Cardiopulmonary bypass was maintained for 60 minutes, and the pigs were monitored for an additional 120 minutes, before sacrifice. The oncotic pressure was maintained and significantly higher in the PrimECC®, group and more fluid were given to the control group to maintain blood pressure.

### 5 Products to be evaluated

PrimECC® is a physiological salt solution containing dextran 1 and dextran 40. The solution is sterile and intended for single use only. PrimECC® is CE-marked and used according to the certified intended use and in line with local clinical routine.

The XVIVO Click Adapter is to be connected to the green click port connector on the bag.

#### 5.1 Test group

The ECC priming solution PrimECC® (the investigational device) will be used to prime the ECC circuit before the start of subject perfusion in the test group.

#### 5.2 Control group

The standard crystalloid ECC circuit priming solution (the comparator) used at the participating centers i.e., Ringer's acetate with or without mannitol will be used to prime the ECC circuit before the start of subject perfusion in the control group. A mix of two crystalloid priming solutions is allowed. The

standard solution is CE-marked (if classified as medical device) or has a Marketing Authorization and is used according to the certified intended use or within the scope of the Marketing Authorization.

Colloid priming solutions are not allowed in the study but could be administered to the subject as clinically indicated.

### 5.3 Volume of priming solutions

The ECC priming volume should be according to the standard of care at the respective participating clinic. The typical priming volume is between 1000ml and 1500ml. The same volume of solution must be used for priming the ECC machine in both arms of the study (test group and control group). If additional volume is administered to the subject after priming the ECC machine and during the perfusion of the subject, crystalloid solution should be used and not additional PrimECC®.

### 5.4 Method of priming

Priming of the ECC should be done according to standard of care at the respective participating clinic.

Retrograde autologous priming (RAP) where the subject's systematic pressure is used to replace the crystalloid solution with autologous blood is not to be used in the study as this method reduces the net priming volume.

### 5.5 Instruction for use PrimECC®

#### Description

PrimECC® is a CE-marked physiological salt solution containing dextran 1 and dextran 40. The solution is sterile and intended for single use only.

PrimECC® is supplied in bags equipped with a port system with one twist off port for injection and one twist off port with click connector for administration. The material in the bag is a multilayer foil consisting of polypropylene, polyethylene, and polyester. Each bag is sealed in an outer polypropylene/polyamide bag. The XVIVO Click Adapter is to be connected to the green click port connector on the bag.

#### Intended purpose

PrimECC® is intended as a priming solution for the extracorporeal circulatory (ECC) circuit prior to connecting it to the patient's circulation at onset of cardiopulmonary bypass.

PrimECC® is not intended for any other use than stated above.

#### Contraindications

Known hypersensitivity to dextran.

Manifest renal injury with oliguria or anuria.

#### Warning

Do not use PrimECC® if the solution is unclear, the container or outer bag is damaged, or if the 'use by' date has expired.

PrimECC® is intended for single use only and MUST NOT BE REUSED.

Maintain aseptic technique when making any additions as well as during administration.

Do not use the injection port for administration.

### Precautions

PrimECC® is ready to use, no additives are necessary.

The responsibility for correct clinical use and technique rests with the user. The Instructions for Use is only provided as a suggestion for procedure, the user must on the basis of her or his medical training and experience evaluate the suitability of this procedure.

PrimECC® must not be used for fluid therapy pre- or postoperatively. The maximum dosage of 1.5 g dextran 40 per kg body weight must not be exceeded (= 33 ml PrimECC®/kg body weight).

PrimECC® contains lactate which may slightly increase plasma lactate levels (by about 6 mmol/l).

Unfractionated heparin should be used cautiously post-operatively as the interaction with dextran might result in excessive bleeding.

**Pregnancy:** There are no data on the use of PrimECC® during pregnancy. PrimECC® should only be administered to pregnant women if strictly needed.

**Lactation:** It is not known to what extent PrimECC® passes into breast milk. In the absence of human data, breastfeeding may be continued if clearly needed considering the benefit of breast feeding for the child and the benefit of therapy for the woman.

**Treatment of children:** There are no data on the use of PrimECC® on children. PrimECC® should only be administered to children if strictly needed.

### Adverse Effects

Dextran has been associated with rare anaphylactic reactions (<1 in 1000) such as urticaria, fever, chills, pruritus and anaphylaxis.

Any invasive procedure carries a risk of infection.

### Instructions

1. Read and understand all the instructions below before proceeding. A standard, sterile transfer set equipped with a spike, a tubing clamp and a XVIVO Click Adapter are needed for an aseptic transfer of PrimECC® to the extracorporeal circulation system. Use aseptic technique throughout the whole procedure.
2. When the outer bag is removed, check that the container is intact by compressing it. Do not use PrimECC® if the solution is unclear, the container or outer bag is damaged, or if the 'use by' date has expired.
3. Instruction on how to connect the bag to the XVIVO Click Adapter.

#### XVIVO Click Adapter

- I. Remove the XVIVO Click Adapter from its sterile packaging.
- II. Connect the XVIVO Click Adapter to a tubing set.
- III. Clamp the tubing set.
- IV. Twist off the closing cap of the green click port on the bag (Picture 1).

[figure not shown]

Picture 1

- V. Remove the protection cap on the connector of the XVIVO Click Adapter. Push the connector of the XVIVO Click Adapter into the green click port on the bag until it is locked (Picture 2).

[figure not shown]

Picture 2

- I. For removal of the XVIVO Click Adapter, press the side-wings of the XVIVO Click Adapter and pull out the connector (Picture 3).

[figure not shown]

Picture 3

### How supplied

PrimECC® is supplied as 6\*1600 ml bags and 6\*XVIVO Click Adapters per carton.

Store between +2– +25°C.

### Symbols

|                                                                                     |                                                                                                         |
|-------------------------------------------------------------------------------------|---------------------------------------------------------------------------------------------------------|
| [figure not shown]   | Sterilized using steam                                                                                  |
| [figure not shown]   | Sterilized using ethylene oxide                                                                         |
| [figure not shown]   | Do not re-use, discard after procedure. Reuse of PrimECC® is not allowed due to the risk for infection. |
| [figure not shown]   | Do not re-sterilize                                                                                     |
| [figure not shown]   | Do not use if the product sterilization barrier or its packaging is compromised.                        |
| [figure not shown]   | Use by                                                                                                  |
| [figure not shown]   | Store between 2–25°C.                                                                                   |
| [figure not shown]   | Caution: Consult accompanying documents.                                                                |
| [figure not shown]   | Batch code                                                                                              |
| [figure not shown]   | Catalogue number                                                                                        |
| [figure not shown]   | Containing dextran 1 and dextran 40                                                                     |
| R x only                                                                 | Caution: Federal US laws restricts this device to sale by or on the order of a physician.               |
| [figure not shown]  | Manufacturer                                                                                            |
| [figure not shown] | Injection Port                                                                                          |
| [figure not shown] | Administration Port                                                                                     |

[www.xvivoperfusion.com](http://www.xvivoperfusion.com)

Manufacturer  

## 5.6 Product distribution

Five boxes of PrimECC® will be sent out at initiation of the trial at each centre. Each centre will request a reasonable amount of product depending on their expected inclusion rate and storage capability at study initiation. Further deliveries will be made as reasonable and upon request, to complete the total number of patients in the trial. Each box of PrimECC® Product ref No 19054 contains six bags of PrimECC® and six click adaptors. One bag and one click adapter is used for each patient.

### 5.7 Product accountability

XVIVO will provide each study centre with the priming solution PrimeECC®. The control group products will be supplied by the study centre in accordance with the current clinical standard at each centre.

The accountability document must be filled in by the person in charge of receiving the study solution at each study centre. The recording method defined and approved during the study initiation visit by the study monitor will be followed throughout the study. Following data are to be recorded for each study product:

- Date of receipt at the study centre
- Batch/lot number
- Expiry date
- Date of use
- Treated patient's study identification
- Date of and reason for return of unused expired or malfunctioning product (if applicable)

## 6 Study Hypotheses and Objectives

### 6.1 Hypothesis

The main hypothesis is that, in a population at high risk for postoperative AKI, priming the ECC circuit with PrimeECC® instead of only crystalloid solution will lead to a reduced rate of postoperative AKI.

The secondary hypothesis is that priming of the ECC circuit with PrimeECC®, compared to a crystalloid solution, will lead to less tubular cell injury, less hemolysis, better fluid balance and better organ preservation.

### 6.2 Primary objective

The primary objective is to evaluate the differential effects of priming with PrimeECC® or crystalloid solution on the incidence of post-operative AKI in a high-risk population.

### 6.3 Secondary objective

The secondary objectives are to study the safety parameters when PrimeECC® is used in a large cohort of patients, especially related to bleeding and anaphylactic events, and to assess renal, and myocardial injury.

### 6.4 Exploratory objective

The exploratory endpoint is to investigate Central nervous system (CNS) injury and NAG/creatinine ratio is a marker to investigate renal tubular impairment.

### 6.5 Primary endpoint

The primary endpoint is incidence of postoperative AKI of any stage according to the KDIGO creatinine criteria (serum-creatinine increase  $\geq 26.5 \mu\text{mol/l}$  within 48 h or  $\geq 50 \%$  increase from baseline) within 96 h after ECC.

### 6.6 Secondary endpoint

The secondary endpoints are differences between groups in

- eGFR, the highest post-operative value within 96 hours after ECC compared to pre-operative (day before surgery), calculated using the CKD-EPI formula.

- Incidence of AKI of different stages according to the KDIGO creatinine criteria within 96 hours after ECC.
- Hemolysis, after induction of anesthesia and at 1-hour after induction of ECC, 1-hour post- ECC and 24 hours post- ECC., measured as plasma free hemoglobin (PfHb).
- Myocardial injury markers, TNI/TNT, after induction of anesthesia and at 1-hour post- ECC and 24 hours post- ECC. TNI or TNT is chosen according to institutional standard.

### 6.7 KDIGO creatinine criteria, staging of AKI

| Stage | Serum creatinine                                                                                                                                                                         |
|-------|------------------------------------------------------------------------------------------------------------------------------------------------------------------------------------------|
| 1     | 1.5- 1.9 times baseline OR $\geq 0.3$ mg/dl ( $\geq 26.5$ $\mu\text{mol/l}$ ) increase                                                                                                   |
| 2     | 2.0- 2.9 times baseline                                                                                                                                                                  |
| 3     | 3.0 times baseline OR Increase in serum creatinine to $\geq 4.0$ mg/dl ( $\geq 353.6$ $\mu\text{mol/l}$ ) OR, in patients <18 years, decrease in eGFR to <35 ml/min per $1.73\text{m}^2$ |

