## 8.11 Postoperative parameters

In addition to the laboratory analysis defined above, the patient fluid balance is registered as the sum of infusion of crystalloids, colloids, transfusions, bleeding and urine output. All infusions of blood and/or plasma products are recorded during the study period. Reoperation for bleeding, time on ventilator, significant infections, and ICU length of stay and hospital length of stay are registered.

Use of mechanical renal support such as continuous renal replacement therapy (CRRT) or hemodialysis is registered during the study period.

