### 9.3 Serious adverse event

A Serious Adverse Event is one that led to anything of the following:

1. death

2. serious deterioration in the health of the subject, that resulted in any of the following

- life-threatening illness or injury,
- permanent impairment of a body structure or a body function,
- hospitalization or prolongation of hospitalization,
- medical or surgical intervention to prevent life-threatening illness or injury, or permanent impairment to a body structure or a body function
- chronic disease
- fetal distress, fetal death or a congenital physical or mental impairment or birth defect

3. A planned hospitalization for a pre-existing condition or a procedure required by this protocol, without a serious deterioration in health, is not considered to be a SAE.

In the study all AKI related events that are requiring any type of intermittent dialysis or continuous renal replacement therapy (CRRT) should be reported as an AE/SAE.

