### 11.7 Missing Data

All data analyses will be performed on data available. A sensitivity analysis to address missing data will be performed for the primary endpoint in the case of more than 5% missing in either treatment group with multiple imputation. No imputation or corrections will be made for missing data for secondary analyses. Every attempt shall be made to obtain data per protocol. Resources to obtain data include patient or coordinator/physician interview, and chart review. Hence, missing data is expected to be minimal.

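### Renal replacement therapy is promised as a secondary outcome and is recorded, but it enters no endpoint, and stage 3 AKI is defined by creatinine alone, so dialysed patients can be under-staged.

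*Protocol*

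**What the plan says.** Section 2 states: "As secondary outcomes, incidence of renal replacement therapy, NAG-excretion and estimated glomerular filtration rate (eGFR) will be evaluated". Section 8.11 provides for the data: "Use of mechanical renal support such as continuous renal replacement therapy (CRRT) or hemodialysis is registered during the study period". Table 1 in Section 7.4 places mechanical renal support at 24 h and on postoperative days 2, 3 and 4. Section 9.3 adds that AKI events "requiring any type of intermittent dialysis or continuous renal replacement therapy (CRRT) should be reported as an AE/SAE".

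The endpoint sections do not take this up. Section 6.5 reads: "The primary endpoint is incidence of postoperative AKI of any stage according to the KDIGO creatinine criteria", and sets the thresholds at a rise of at least 26.5 µmol/l within 48 h or at least 50% from baseline. Section 6.6 lists "Incidence of AKI of different stages according to the KDIGO creatinine criteria within 96 hours after ECC". The stage table in Section 6.7 gives stage 3 as "3.0 times baseline OR Increase in serum creatinine to" at least 353.6 µmol/l, plus an eGFR route for patients under 18. Sections 6.8 and 6.9 do not mention RRT.

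On incomplete data, Section 11.7 says: "All data analyses will be performed on data available". It adds a multiple-imputation sensitivity analysis of the primary endpoint "in the case of more than 5% missing in either treatment group".

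**The concern.** Two things do not fit together. First, an outcome announced in Section 2 and collected throughout follow-up has no place in the endpoint list, so the protocol does not settle whether it will be analysed as an efficacy outcome or will appear only among adverse events.

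Second, the stage table relies on a measurement that the treatment itself alters. Once RRT starts, serum creatinine no longer tracks kidney function. The patients whose injury was judged to need RRT are then those whose creatinine may stop short of the stage 3 thresholds. The top category of a named secondary endpoint can miss the cases it is meant to hold, and the stage distribution would look milder than it is.

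**Working it through.** **1. Section 2 against the endpoint list.** The sentence in Section 2 names three outcomes.

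| Outcome in Section 2 | Where it appears in Section 6 |
|---|---|
| eGFR | 6.6, secondary |
| NAG excretion | 6.8, exploratory |
| Incidence of RRT | nowhere in 6.5, 6.6, 6.8 or 6.9 |

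NAG was given a different rank. RRT has none. This contradiction needs no assumption.

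**2. How a dialysed patient is scored under Sections 6.5 and 6.7.** The under-18 route is closed, because inclusion requires age 18 or over. Pre-operative dialysis is an exclusion criterion, so RRT during follow-up is newly started. Suppose creatinine does not climb further once RRT begins. The stage then depends on the highest value reached:

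- 2.0–2.9 times baseline and below 353.6 µmol/l: stage 2
- 1.5–1.9 times baseline, or a rise of at least 26.5 µmol/l: stage 1
- below both thresholds: no AKI

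Only a patient who reached 3.0 times baseline or 353.6 µmol/l is stage 3.

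**3. Why staging is affected more than any-stage AKI.** Take the baseline at which the two stage 3 routes coincide: 353.6 / 3.0 = 117.9 µmol/l.

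- Stage 1 begins at 117.9 + 26.5 = 144.4 µmol/l.
- Stage 2 begins at 2 × 117.9 = 235.7 µmol/l (unrounded baseline).
- Stage 3 begins at 353.6 µmol/l, a rise of 353.6 − 117.9 = 235.7 µmol/l.

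RRT must begin within the first 26.5 µmol/l of the rise for AKI to be missed altogether. It can begin anywhere in the 235.7 µmol/l below stage 3 and leave the patient under-staged. Also, 26.5 / 0.50 = 53 µmol/l, so above that baseline the absolute criterion (within 48 h) is easier to meet than the 50% criterion.

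**4. Whether Section 11.7 helps.** It addresses missing data. A dialysed patient with creatinine values is observed, though misleadingly, so imputation does not apply.

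**5. The plan's sample size.** Section 6.10 gives 366 for 50% v 35%, Fisher's test, 80% power, α = 0.05. With 1:1 allocation assumed, the two-sided two-proportion formula gives 169.3, so 170 per arm. With continuity correction, 169.3/4 × [1 + √(1 + 4/(169.3 × 0.15))]² = 182.4, so 183 per arm and 366 in total. Exact Fisher power is 79.9% at 182 per arm and 80.3% at 183. The stated figure reproduces and this point does not change it.

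**6. Possible size for the primary endpoint (rates assumed).** An RRT rate of 2–5% is 0.02 × 183 = 3.7 to 0.05 × 183 = 9.2, about 4 to 9 patients per arm. The planned difference is 0.15 × 183 = 27 patients. Each dialysed patient scored as no AKI moves an arm's rate by 1/183 = 0.55 percentage points. Exact Fisher results with 183 per arm:

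| Assumed misclassification | Result |
|---|---|
| 2% / 5% / 10% of AKI cases missed in each arm | power 78.7% / 76.3% / 72.2% |
| 1 / 2 / 3 points missed in each arm | power 80.4% / 80.6% / 80.8% |
| 1 / 2 / 3 points missed in control only | power 74.5% / 67.8% / 60.6% |
| No true effect (50% in both arms), nothing missed | rejection 4.1% |
| No true effect, one arm loses 1 / 2 / 3 / 5 points | rejection 4.5% / 5.6% / 7.6% / 14.0% |

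Losses that are similar in both arms and confined to a few cases cost little. The one-arm rows need nearly all dialysed patients in one arm to be scored as no AKI, which step 3 makes unlikely.

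**The case against.** The strongest defence is that the protocol labels its definition as creatinine-based in Sections 6.5, 6.6 and 6.7, so for the primary endpoint this is an open choice. RRT is not lost either: it is recorded and reported as an adverse event. Creatinine is measured at 1 h and 24 h and on days 2 to 4, so few dialysed patients should escape the any-stage criterion. The trial is blinded, and nothing suggests that misclassification would differ between arms. All of this stands, and it limits the consequence for the primary endpoint. It does not explain why an outcome named in Section 2 is absent from Section 6, nor does it correct the stage assigned to a dialysed patient.

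A reader might infer two stronger claims. The first is that the primary contrast is biased. That needs misclassification that depends on arm, which the documents do not show.

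The second is that patients who die or leave before 96 h are scored AKI-free on whatever creatinine exists, so the 5% trigger would hardly fire. Section 11.7 does not say so. Excluding such patients is an equally open reading, and rules on evaluability and death may be set in the SAP, which is not at hand. Early departure is also not a marker of the most severe injury. An example can be built: with 9 test-arm patients missing, 68/174 v 92/183 gives p = 0.043, and p = 0.142 if all 9 had AKI (77/183). But it puts every missing patient in one arm, at the highest count still significant. At the planned 35% (61/174), significance survives even if all 9 had AKI (70/183, p = 0.027).

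**Conclusion.** The point holds for RRT. Section 2 and Sections 6.5 to 6.9 disagree on whether RRT incidence is an outcome, and the stage table can place a dialysed patient in stage 1 or 2, or occasionally in no AKI. The AKI-by-stage secondary endpoint bears most of this. The effect on any-stage AKI is probably small, and the sample size of 366 is unaffected.

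The contradiction and the scoring rest on the text, together with the general fact that RRT lowers creatinine. The size rests on assumed RRT rates, because the documents give none. How deaths and early departures before 96 h are handled is not part of this conclusion.

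**What to change.** Three changes of wording, all about classifying the outcome and none about patient care:

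1. In Sections 6.5 and 6.7, count RRT started within 96 h after ECC as AKI stage 3.
2. In Section 6.7, state that creatinine measured after RRT start is not used to lower the stage.
3. In Section 6.6, list incidence of RRT within 96 h as a secondary endpoint, so that it agrees with Section 2.

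RRT use and creatinine are already collected. Rules 1 and 2 need the start time of RRT. Table 1 marks only visits, so the eCRF should be checked for that field; the adverse event report already requires a start date. The downside is that the endpoint is no longer purely creatinine-based, and a few patients dialysed for non-renal reasons may be counted as stage 3. Reporting the creatinine-only version alongside would keep the present definition visible.
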